## Abstract

Evidence is limited on an early treatment strategy for any type of recent-onset atrial fibrillation (AF), comparing anti-arrhythmic drug (AAD) therapy to catheter ablation of patients presenting to the emergency department (ED). The purpose of the EMERGE Cryo study is to investigate the impact of early catheter ablation in patients presenting to the ED with recent-onset AF.

The EMERGE Cryo study is a prospective, 2-arm, randomized, open-label, blinded endpoint, multicentre study to investigate the impact of first-line ablation vs AAD in patients presenting to the ED (within the preceding 2 weeks) with recent-onset (≤ 1 year) paroxysmal or persistent AF (longest AF episode < 6-month duration). All study participants receive an implantable loop recorder. Randomization is based on a 1:1 ratio into 2 study arms: (i) cryo-AF-ablation: pulmonary vein isolation performed with cryoballoon; and (ii) usual care: AAD therapy, including electrical cardioversion, if necessary. A total of 350 patients will be randomized.

Both arms have a blanking period or an AAD optimization period of 3 months, during which adapting the therapy will be allowed. This trial is designed to elaborate whether early AF ablation is superior to usual care. The primary effectiveness endpoint is freedom from any atrial tachyarrhythmia (> 30 seconds) through 3-12 months of follow-up on implantable loop recorder monitoring. Patients will be followed up for 36 months in total.

EMERGE Cryo aims to determine the value of early catheter ablation in AF patients presenting with any type of AF to the ED.

**Clinical Trial Registration:**

NCT05294445.

Atrial fibrillation (AF) is the most frequent cardiac arrhythmia in adults,^1^ and it is associated with increased mortality and morbidity. The occurrence of AF is related to a wide variation of symptoms and is a common reason for patients to present to emergency departments (EDs), leading to hospitalizations and high healthcare costs.^2^^,^^3^ Approximately 70% of the patients who are hospitalized for AF are admitted via the ED.^4^^,^^5^ The steady increase of AF-related visits to EDs thereby leads to a high number of hospitalizations.^1^

Catheter ablation therapy has been proven to be safe and effective for the treatment of symptomatic paroxysmal AF and is now the standard for AF therapy.^6^, ^7^, ^8^ Several trials have shown that catheter ablation in this setting is superior to antiarrhythmic drug (AAD) therapy in maintaining sinus rhythm.^9^^,^^10^ As evidenced by the Cryoballon or Radiofrequency Ablation for Paroxysmal Atrial Fibrillation (FIRE & ICE trial), cryoballoon ablation is noninferior to the former gold standard of radiofrequency current energy ablation.^11^ An important finding is that cryoballoon ablation is associateed with a reduction in resource use.^12^

Data on the optimal timing of AF ablation are scarce. Recently, early rhythm control of AF has been shown to be beneficial in preventing negative cardiovascular outcomes.^13^ In a subanalysis of the Early Treatment of Atrial Fibrillation for Stroke Prevention (EAST-AFNET-4) study, symptomatic and asymptomatic recent-onset AF patients derived equal benefit from early rhythm control.^14^

Although catheter ablation has proven to be effective in delaying progression from paroxysmal to persistent AF,^15^ only a few trials have evaluated early AF treatment strategies in relation to patients' medical histories (cryoablation vs. antiarrhythmic drugs: first-line therapy for patients with paroxysmal atrial fibrillation [CRYO-FIRST],^16^ Cryoablation or Drug Therapy for Initial Treatment of Atrial Fibrillation [EARLY-AF],^17^ Cryoballoon Ablation as Initial Therapy for Atrial Fibrillation [STOP-AF FIRST]^18^). Another study examined the implementation of a multidisciplinary AF treatment pathway in ED patients, demonstrating reduced admission rates and hospital stays; however, this approach did not include catheter ablation.^5^

To date, no robust scientific evidence has been gathered from large-scale studies comparing early catheter ablation vs antiarrhythmic drug therapy in AF patients presenting to the ED with recent-onset AF, including those experiencing a first episode. Additionally, the impact of catheter ablation in patients with persistent AF has not been investigated in sufficient detail, as reflected by the current guideline recommendation.^1^

Given that the relevance of AF burden as a study endpoint has gained increasing clinical awareness, continuous follow-up via an implantable loop recorder is considered an essential component of current AF study designs.^19^^,^^20^

Therefore, the purpose of the From the Emergency Department, Directly to Ablation of Atrial Fibrillation (EMERGE Cryo) study is to evaluate the efficacy and safety of an early rhythm control treatment of recent-onset AF by catheter ablation with the cryoballoon vs usual care (AAD), with respect to arrhythmia recurrence, rehospitalization, and heart failure, in patients presenting to the ED or as an emergency visit in an outpatient clinic.

## Methods

### Study design

The EMERGE Cryo study is an investigator-initiated, prospective, 2-arm, randomized, open-label, blinded endpoint, multicentre study to investigate the impact of first-line ablation in patients presenting to the ED or as an emergency visit in an outpatient clinic with recent-onset paroxysmal or persistent AF, including patients with a first episode of AF. According to the statistical analysis plan, n = 350 patients will be enrolled at up to 13 German centres. Each site will contribute < 50% of subjects.

This study has been approved by regional ethics committees and is conducted in accordance with the Declaration of Helsinki and the International Council for Harmonisation Good Clinical Practice guidelines. Written informed consent was obtained from all patients. The trial is registered on ClinicalTrials.gov (NCT05294445).

The principal investigator (PI), and Asklepios Proresearch Institute was responsible for the development of the study protocol. The trial is supported by a steering committee. An independent data and safety monitoring board guides the trial. All serious adverse events and study endpoints are assessed by a blinded core lab and adjudicated by an independent endpoint review committee (ERC), which will be blinded to the randomization group.

The contract research organization RQM+ provides support with regard to monitoring of patient data, site supervision, site initiation, and closeout visits. The contract research organization and the study sites use secuTrial (interActive Systems GmbH, Berlin, Germany) as the electronic case-report form system.

### Endpoints

The *primary effectiveness endpoint* is freedom from any atrial tachyarrhythmia, including AF, atrial flutter, and atrial tachycardias (> 30 seconds [s]) through 3 to 12 months of follow-up on implantable loop recorder [ILR] monitoring, or any 12-lead electrocardiogram [ECG] on visits, ECG Holter monitoring, or on symptom-driven event monitoring).

This trial is designed to demonstrate that early AF ablation is superior to usual care in patients presenting to the ED because of AF, with respect to clinical treatment success, which is defined as freedom from atrial arrhythmias (> 30 seconds) through 3-12 months of follow-up care.

Both arms will have a blanking period or an AAD optimization period of 3 months, during which therapy adaptation will be allowed. A repeat ablation procedure will not reset the blanking period. AF occurring during the blanking period, as well as any interventions started during the blanking period, do not count as chronic treatment failures. Study endpoints will be adjudicated by a blinded core laboratory responsible for ILR data analysis, in conjunction with the study's independent ERC. Safety outcomes are not subject to any blanking.

### Secondary effectiveness endpoints of the EMERGE Cryo study are as follows:

•AF burden between 3-12 months after randomization; AF burden is defined as the percentage of time the study participant is in AF during the observation period;•AF burden between 0-3, 3-6, and 6-12 months after randomization;•freedom from AF (> 30 seconds) through 3-12 months of follow-up care;•freedom from atrial tachycardia and atrial flutter (> 30 seconds) through 3-12 months of follow-up care;•analysis of amount of symptomatic vs asymptomatic atrial tachyarrhythmia recurrences through 3-12 months of follow-up care (reported as number of recurrence episodes);•rehospitalization rate due to cardiovascular disease (AF, worsening of heart failure, cardiovascular disease);•progression of heart failure defined as trend in left ventricular ejection fraction and trend in brain natriuretic protein;•improvement of quality of life (QoL) at 12 months compared to baseline (**A**trial **F**ibrillation **E**ffect on **Q**uali**t**y-of-life [AFEQT] questionnaire and EuroQol 5-dimension, 5-level [EQ-5D-5L] questionnaire); and•safety / complications: device- and procedure-related adverse events, serious adverse events, and cardiovascular-related adverse events will be collected to determine and compare the safety profile of the 2 treatment groups.

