### Trial flow

At baseline, an ECG, a transthoracic echocardiogram, a QoL questionnaire (EQ-5D-5L and AFEQT), as well as certain blood tests will be performed for every patient. Randomization takes place at baseline. Patients who are in the intervention group will receive cryoballoon-guided AF ablation within 21 days from baseline. Patients who are in the control group will receive standard-of-care only, which is defined as a rhythm control strategy with electric cardioversion (if necessary) and AAD. Both arms will receive an ILR for continuous rhythm monitoring. Regular follow-up evaluation is planned for both groups after 3, 6, and 12 months. An extended follow-up evaluation of the ILR events up to 24 and 36 months is planned, including a patient phone call at 24 and 36 months for detection of adverse events, and QoL assessment (sent via letter).

Randomization is based on a 1:1 ratio into 2 study arms, as follows: (i) cryo AF ablation—pulmonary vein isolation (PVI) performed with a cryoballoon ablation system; and (ii) usual care—AAD therapy based on the decision of the investigator according to current European Society of Cardiology (ESC) guidelines,^1^ including electrical cardioversion, if necessary. Both arms will have a blanking period or an AAD optimization period of 3 months, during which adaptation of the therapy will be allows (Fig. 1).

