### Usual care group

Patients randomized into the usual care group should start or be maintained on antiarrhythmic drug therapy within 21 days, based on the decision of the investigator, according to current ESC guidelines.^1^ Usually, class Ic AAD (eg, flecainide, propafenone) will be used apart from patients with comorbidities and/or impaired left ventricular function, who will preferably receive amiodarone. If necessary, cardioversion can be performed to establish sinus rhythm according to current ESC guidelines.^1^ Oral anticoagulation and treatment of comorbidities will be performed at the discretion of the investigator, according to current guidelines, for both study arms.^1^

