### Statistical methodology

The study’s statistical analysis plan outlines the following: The primary analysis is related to atrial tachyarrhythmias and AF. A survival table and a Kaplan-Meier plot with stratified survival curves by groups will be shown. A log-rank test will be applied to examine differences of the hazard function between the treatment groups. A *P*-value of < 0.05 will be considered significant.

Secondary analyses are associated with QoL, left ventricular ejection fraction, and brain natriuretic protein over time. (Generalized) linear mixed models will be used to examine differences between ablation groups. AF burden and the rehospitalization rate will be analyzed descriptively. The time to first rehospitalization will be presented as survival tables and plots. Secondary endpoints were considered exploratory.

Procedure-related complications, including the index and any repeat catheter ablation, ILR implantation, and cardioversion, will be observed. As the serious adverse events are captured in free text, they will be harmonized (by the trial steering committee) before analysis. Each single type of adverse event for a subject will be shown only once.

All serious adverse events, and their duration, resolution, cardiac cause, and severity are listed. The summary table comprises only the treatment-related adverse events with a cardiac cause.

The regular study phase concludes after 12 months, including site monitoring as well as ERC and data and safety monitoring board oversight. During the subsequent prolonged follow-up period (up to 24 and 36 months), rhythm-related endpoints via ILR, and serious adverse events, will continue to be collected.

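### The safety comparison has a category for device- and procedure-related events but none for antiarrhythmic-drug-related events, so non-serious, non-cardiovascular drug reactions have no place in it

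*Protocol article*

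**What the plan says.** All references are to the Protocol article.

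- **Secondary effectiveness endpoints, last item.** The safety comparison is built from three categories: "device- and procedure-related adverse events, serious adverse events, and cardiovascular-related adverse events will be collected to determine and compare the safety profile" of the two treatment groups.
- **Trial flow.** The control group receives standard of care, "which is defined as a rhythm control strategy with electric cardioversion (if necessary) and AAD".
- **Usual care group.** "Patients randomized into the usual care group should start or be maintained on antiarrhythmic drug therapy within 21 days". Class Ic agents are the usual choice, with amiodarone preferred where there are comorbidities or impaired ventricular function.
- **Statistical methodology.** Three statements deal with safety output: "Procedure-related complications, including the index and any repeat catheter ablation, ILR implantation, and cardioversion, will be observed"; "All serious adverse events, and their duration, resolution, cardiac cause, and severity are listed"; and "The summary table comprises only the treatment-related adverse events with a cardiac cause". The same section says of the whole secondary family: "Secondary endpoints were considered exploratory".
- **Table 2.** An adverse-event reporting row, with no restriction by type of event, is marked for both arms at baseline and at 3, 6 and 12 months. It is also marked at ablation and pre-discharge, which are ablation-group columns.

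**The concern.** The trial compares a procedure with a drug. One of the three safety categories is defined by relation to treatment, and it fits only the procedural side: it takes in device and procedure events however minor. A drug event enters the comparison only if it is serious or cardiovascular. Minor events are thus admitted under different rules depending on which treatment caused them.

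At stake is whether the safety comparison is even-handed. The Introduction gives safety, alongside efficacy, as part of the study's purpose, and the tolerability of long-term drug treatment belongs to that question. If minor procedural events count and minor non-cardiovascular drug reactions do not, usual care will tend to look better tolerated relative to ablation than it was.

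**Working it through.** The article states no figure that bears on this point, so the check is a reading of every safety rule against each kind of treatment-related event.

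**Step 1: classes of event.** Cross the cause (device/procedure or drug) with seriousness and with cardiovascular nature: 2 × 2 × 2 = 8 classes.

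**Step 2: rule from the endpoint list.** A class has a place if it is device- or procedure-related, OR serious, OR cardiovascular.

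| Class | Device/procedure-related | Drug-related |
|---|---|---|
| Serious, cardiovascular | yes | yes |
| Serious, non-cardiovascular | yes | yes |
| Non-serious, cardiovascular | yes | yes |
| Non-serious, non-cardiovascular | yes | **no** |

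Coverage is 4 of 4 for device/procedure and 3 of 4 for drug, so 7 of 8 overall.

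**Step 3: does the Statistical methodology section restore the missing class?** Take a mild gastrointestinal, thyroid or liver reaction to an AAD.

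- *Complications sentence:* it names ablation, loop-recorder implantation and cardioversion. A drug reaction is none of these.
- *Listing:* it covers serious events. The reaction is not serious.
- *Summary table:* the treatment-related label can include drugs, but the table is limited to a cardiac cause. The reaction is not cardiac.

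None of the three takes it in. A minor non-cardiac procedural event is taken in by the complications sentence. If cardiac cause is read as equivalent to cardiovascular, this section also covers 7 of 8 classes, with the same one missing.

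**Step 4: direction.** Ablation is the assigned treatment in one arm and drug therapy in the other, so the omitted reactions should fall mainly in usual care. The split is not clean. Loop-recorder implantation takes place in both arms, cardioversion can occur in either, and the article does not bar AADs after ablation, where therapy may be adapted during the first 3 months.

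**Step 5: size.** The 8 classes are cells in a grid, not patients or events. The article gives no adverse-event rates and defines no pooled any-event rate, so no difference between arms can be calculated.

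**Step 6: how far the trial has run.** The Study setting and timeline section gives 319 patients enrolled of 350 planned, as of 15 August 2025: 319 / 350 = 91.1%.

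**The case against.** The strongest reply is that this is one bullet in a condensed article. Event categories, causality rules and by-arm tables are normally left to the full protocol, the case report form or the analysis plan, none of which is shown. The bullet does not say that other events are excluded, and Table 2 has an unrestricted adverse-event row for both arms. Part of this stands: a fuller document may define drug-related events, and such reactions may well be recorded. But the article is not silent. It states what the safety comparison is made of, and it describes the complications, the listing and the table that follow. Read together, these admit minor procedural events and leave out the matching drug events. If the full protocol differs, the printed endpoint should be brought into line with it.

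The second reply is that the effect is small, and this stands almost entirely. The uncovered class must be non-serious, non-cardiovascular and drug-related all at once, within an exploratory endpoint. Proarrhythmia and all serious drug reactions are covered.

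Three stronger readings are tempting, and the article does not support them:

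- *The summary table is lopsided.* It is not. Its limit to a cardiac cause removes non-cardiac events of both treatments alike. The imbalance lies in the endpoint list and the complications sentence.
- *The 3-month optimization period hides early drug reactions.* The Endpoints section says that safety outcomes are not blanked.
- *The gap flatters ablation.* The direction is the opposite. It understates harm in the comparator and so works against the arm whose superiority is being tested.

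**Conclusion.** The point holds in a narrow form and is minor. As printed, the safety comparison has a relatedness category for devices and procedures at any level of seriousness and none for AADs. Non-serious, non-cardiovascular drug reactions therefore fall outside every stated safety comparison, while procedural events of the same kind are included. The tendency is to understate usual-care harm.

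Its size cannot be determined from the article. A reader might infer that the trial's safety conclusions or its main result are in doubt. Neither follows, because serious events, cardiovascular events and the primary endpoint are untouched.

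The conclusion rests on two assumptions: that the printed list is the list used for the comparison, and that drug reactions arise mainly, though not only, in usual care.

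**What to change.** 1. In the safety item of the secondary endpoints, begin the list with *device-, procedure- and antiarrhythmic-drug-related adverse events*, and leave the other two categories as they are.
2. In Statistical methodology, add one table of treatment-related adverse events of any cause, by arm, beside the procedural complications. Apply the same relatedness rule in both arms, and count drug reactions in whichever arm they occur.
3. Limit that table to the 12-month study phase, because after it only "rhythm-related endpoints via ILR, and serious adverse events, will continue to be collected".

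The cost is wording in two places and one table, with no new visits, provided that sites used the Table 2 adverse-event row for all events. That proviso needs checking with the sponsor. If sites recorded only the categories in the printed list, non-serious drug reactions will be under-recorded in the 319 patients already enrolled, and the report must state this as a limitation. Even on the favourable reading, the first scheduled report after the drug is started in usual care is at 3 months, whereas the ablation group also has reports at ablation and before discharge. Minor early drug reactions may therefore be missed. The reported usual-care event count may rise, which is the purpose of the change. Separate laboratory or drug-discontinuation analyses are optional and are not needed to close this gap.

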### Study setting and timeline

As of August 15th, 2025, a total of 13 sites in Germany have been activated or have pending activation, with a total of 319 patients enrolled. We aim to complete enrollment of 350 patients within 4 months (by October 2025). Appendix Material S1 and S2.

### Patient population

Inclusion criteria include recent-onset (≤ 1 year prior to enrollment) documented paroxysmal or persistent AF (longest AF episode < 6-month duration), presenting at the ED or an outpatient clinic as an emergency visit within the preceding 2 weeks because of AF, including patients with spontaneous conversion to sinus rhythm (with prior AF documentation). This group also includes patients presenting with their first clinical episode of AF, and patients with both symptomatic and asymptomatic AF. Patients meeting the study inclusion and exclusion criteria as listed in Table 1 will be screened, by the investigator or the investigator’s designee, from the investigator’s general patient population. Patients who meet the enrollment criteria and sign the informed consent form will be included in the study.

**Table 1 tbl1:** Inclusion and exclusion criteria

Inclusion criteria:
• documented paroxysmal or persistent AF (longest AF episode < 6-month duration). Any ECG documentation of AF (12-lead ECG, Holter ECG, or mobile ECG monitoring) needs to be presented. • recent-onset AF (≤ 1 year prior to enrollment) • presenting at the emergency department or outpatient clinic within the last 2 weeks because of AF, including patients with spontaneous conversion in sinus rhythm (with prior AF documentation) • age ≥ 18 years • subject is able and willing to give informed consent
Exclusion criteria:
• persistent AF > 6 mo (1 episode) • LA diameter > 60 mm • severe mitral stenosis or regurgitation, prior mitral valve reconstruction or replacement • any previous LA ablation • ongoing continuous AAD therapy with amiodarone at baseline • history of failed continuous AAD therapy with > 1 agent. Exceptions are beta-blocker, verapamil, or “pill in the pocket” therapy • any condition or disease, which is a contraindication for AF ablation, per the assessment of the investigator • any condition or disease, which is a contraindication for AAD treatment, per the assessment of the investigator • known intracardiac thrombus formation under continuous oral anticoagulation (defined as intake > 4 wk) • any contraindication for oral anticoagulation • any untreated or uncontrolled hyperthyroidism or other reversible causes for AF, such as alcoholism • pregnant or breastfeeding woman or woman of childbearing potential not on adequate birth control • active systemic infection • coexistence of non-PV-dependent atrial tachycardia∗

AAD, anti-arrhythmic drug; AF, atrial fibrillation; ECG, electrocardiogram; LA, left atrial; PV, pulmonary vein.

∗ This includes any prior ECG of focal atrial tachycardia, atypical atrial flutter, and/or atrioventricular (node) re-entrant tachycardia.

